#### 2.10.2. Secondary outcome.

The changes in depression, anxiety, sleep quality and quality of life scores before and after duloxetine treatment in patients with CAPS and their relationship with changes in miRNA.

### 2.11. Data collection

#### 2.11.1. Questionnaire.

HAMA Generalized Anxiety Disorder7/Hamilton Depression Scale Patient Health Questionaires 9: reflect subjects’ psychological status (anxiety/depression)

Pittsburgh sleep quality index: Pittsburgh sleep quality index. To evaluate sleep quality score

Short Form 36: Short form 36. To evaluate quality of life score

Numerical Rating Scale: Numerical Rating Scale. To evaluate change in severity of abdominal pain before and after duloxetine treatment

PRS: To evaluate whether duloxetine dose adjustment was required.

Morisky questionnaire: To evaluate medication adherence.

#### 2.11.2. Physical measurements.

Standardized measurements of heart rate and weight will be performed and blood pressure will be measured by electronic sphygomanometer in order to minimize the potential data deviation and gain realistic data.

#### 2.11.3. Laboratory measurements.

In Clinical Laboratory of Shanghai Ruijin Hospital, blood routine and biochemical indicators will be tested. In laboratory of Gastroenterology, based on the experimental method of Real-Time Fluorescence Quantitative PCR, the miRNA will be sequenced.

### 2.12. Statistical analysis

#### 2.12.1. Sample size calculation.

Taking the bilateral test α = 0.05 and 1-β (power of test) = 0.95, the total sample size of the patients group is 172 cases. According to the 20% shedding or elimination possibility, the sample size of patients group is 215 cases. According to the allocation 1:1, the healthy control group is 215 cases.

#### 2.12.2. Data analysis.

Statistical Package for the Social Sciences for Mac book air, version 26 will be used for data analysis. For descriptive statistics, we use proportions for categorical variables, mean ± SD for normal continuous data, median for non-normally continuous data. K-S tests will be used for the normality test. Descriptive statistic is used to describe the demographic characteristics and laboratory test results. Whole data of primary and secondary outcomes are repeated measure and continuous data. X2 test is used for comparison at different time points and intergroup differences in term of baseline data. If the difference is detected statistically significant, post hoc multiple pairwise comparison will be performed. The association of blood biomarkers, plasma concentration, genotype and clinical efficacy, medication adherence will be assessed by Spearman correlation analysis. *P* < 0.05 is considered statistically significant.

We use intention to treat and per protocol to deal with missing values, outlier values, lost follow-up and non-adherence respectively.

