## Abstract

**Methods/design::**

In this prospective cohort study, we plan to enroll 430 participants including 215 CAPS patients and 215 healthy controls. The CAPS group takes duloxetine 30 mg per day as an initial dose. Patients will have 24-week medication period and follow up at week 0, 4, 12, 24 and 36. Blood samples will be obtained from patients at every visits and health controls at the initial visit and a series of questionnaires will be completed by the participants. The primary end points are: The differential expression of miRNAs between CAPS groups and healthy control groups at baseline. The changes in abdominal pain scores before and after duloxetine treatment in patients with CAPS and their relationship with the changes in miRNAs. The secondary end point is the changes in scores of depression, anxiety, sleep quality and quality of life before and after duloxetine treatment in patients with CAPS and their relationship with changes in miRNAs.

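### The only test named for comparing groups and time points is a chi-square test, which does not fit outcomes the protocol itself calls continuous and repeated

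*Protocol article*

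**What the plan says.** Two neighbouring sentences of section 2.12.2 carry the point. The first describes the data: "Whole data of primary and secondary outcomes are repeated measure and continuous data". The second assigns the test: "X2 test is used for comparison at different time points and intergroup differences in term of baseline data". Post hoc pairwise comparisons follow if the result is significant.

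No t-test, rank test, analysis of variance, Friedman test or mixed model appears anywhere in the article. A Kolmogorov-Smirnov normality check is listed beside the descriptive statistics, but no choice of test depends on it. Spearman correlation is named for associations only.

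Section 2.10.1 gives the primary outcomes: miRNA expression in CAPS patients against healthy controls at baseline, and the before-after change in pain score together with its relation to miRNA change. On sampling, the abstract says "Blood samples will be obtained from patients at every visits and health controls at the initial visit". Section 2.12.1 gives the sizing as "Taking the bilateral test α = 0.05", "1-β (power of test) = 0.95" and "the total sample size of the patients group is 172 cases".

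**The concern.** A Pearson chi-square test compares counts in categories and assumes independent observations. The outcomes are described as neither categorical nor independent.

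- **Pain and the other scales over visits.** The same patients are scored at weeks 0, 4, 12, 24 and 36. A chi-square table of score by visit treats one patient's visits as different people. It makes no use of the fact that 7 is worse than 6, and it does not estimate how far pain fell.
- **Baseline miRNA.** This is a comparison of two independent groups, so there is no pairing to lose. Expression would still have to be cut into classes, and no cut-points are given. That discards information and leaves the cut-points open to choice after the data are seen.
- **The description of the data.** Controls give blood once, so the case-control miRNA comparison is not a repeated measure, although the text says all outcome data are.

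What is at stake is the test behind the first primary outcome and behind the pain-change part of the second, plus the changes in the secondary scales.

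**Working it through.** **1. The plan's own figures.** 172 / (1 − 0.20) = 215, and 1:1 allocation gives 215 controls, so both reproduce. The 172 itself cannot be derived, because no effect size, SD or test is stated. Several inputs return it at two-sided 0.05 and 95% power:
- Two-sample t-test: d = (1.960 + 1.645) × √(2/172) = 0.389; at d = 0.39 the exact t calculation needs 171.8 per group.
- Paired t-test: standardised change 0.276.
- Chi-square with 2 df: noncentrality 15.443 / 0.30² = 171.6, so 172.

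The stated 95% therefore cannot be tied to any one test.

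**2. Baseline miRNA.** Assumptions: normal expression, 172 per group, d = 0.39. The t-test has 95% power. With a median split, the proportions above the cut are Φ(0.195) = 0.577 and 0.423. The noncentrality is 172 × 4 × (0.577 − 0.5)² / 0.5 ≈ 8.2 on 1 df, which gives power of about 82%. Simulation gives 79 to 80%. With 3, 4, 5 and 10 equal classes the power is 82%, 80%, 78% and 67%. A median split would need 271 per group for 95%.

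**3. Pain with no true change.** If both visits are cut at the median, the two binary values correlate at φ = (2/π) × arcsin(ρ). The unpaired test overstates the variance by a factor 1/(1 − φ), so its true size is P(χ²₁ > 3.84/(1 − φ)).

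| Correlation ρ | φ | Size by formula | Size by simulation |
|---|---|---|---|
| 0.3 | 0.19 | 2.9% | 2.8% |
| 0.5 | 0.33 | 1.6% | 1.3% |
| 0.7 | 0.49 | 0.6% | 0.6% |

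On a rounded 0-10 scale at ρ = 0.5, the full 11 × 2 table rejects about 2.3 to 2.9% and the dichotomised score about 1.7%. The error is on the conservative side throughout.

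**4. Pain with a true change.** Assumptions: 172 pairs, two visits, NRS mean 6, SD 2, ρ = 0.5, scores rounded to 0-10. For a 0.5-point change, the SD of the difference is 2 × √(2 × 0.5) = 2, so the paired test has noncentrality 0.25 × √172 = 3.28 and power Φ(3.28 − 1.96) ≈ 91% before rounding.

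| True change | Paired test | Chi-square, 11 × 2 | Chi-square, dichotomised |
|---|---|---|---|
| 0.5 point | 88% (simulated) | 17% | 43% |
| 1 point | near 100% | 93% | 98% |

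For the 1-point change the paired noncentrality is 0.5 × √172 = 6.56. At 1.5 points or more both chi-square versions reach about 100%.

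**5. Dependence on the correlation.** Suppose instead that the change is the one a paired test detects with about 95% power. Median-split chi-square power is then 81%, 68%, 52%, 28% and 14% at correlations 0, 0.3, 0.5, 0.7 and 0.8.

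**The case against.** The wording is loose, and kinder readings exist. The closing reference to baseline data might confine the group comparison to baseline characteristics, where chi-square suits categorical items. A chi-square across time points followed by pairwise comparisons might mean a Friedman test, whose statistic is referred to a chi-square distribution. Neither reading removes the need for a correction. If the whole sentence is confined to baseline data, no test is named for pain change, and baseline miRNA still falls under it. If Friedman is meant, the text does not say so, and that test cannot compare cases with controls.

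A reader might infer that most of the stated power is lost. The documents do not support that. They give no effect size, SD, correlation, cut-points or sizing test, and 172 is itself a possible chi-square sample size. The miRNA comparison keeps roughly 67 to 82% under the assumptions above. The large loss for pain depends on a small true change or a high correlation, and it nearly vanishes at 1 point. The introduction cites 71% effectiveness of duloxetine in CAPS. That is not a mean change in score, but it gives no reason to expect only half a point.

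A reader might also infer that both primary outcomes are tested invalidly throughout, or that false positive pain results would follow. Neither holds. The relation of miRNA change to pain change is assigned to Spearman correlation, which keeps order. Pairing is irrelevant to baseline miRNA. Ignoring pairing for pain makes the test conservative.

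An article may leave model details to a full analysis plan. Here, however, a test is named, and it is the wrong one for the data just described. That is an error in the text and not an omission.

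**Conclusion.** Wrong as written. The named test contradicts the data type stated one sentence earlier, and this holds whatever the power figures are. For pain and the secondary scales, the literal rule ignores pairing, order and magnitude. For baseline miRNA it forces an unspecified categorisation. The claim that all outcome data are repeated is also wrong for the case-control comparison.

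The size of the harm can only be illustrated. It ranges from slight to severe for pain, depending on the true change and the within-patient correlation, and is moderate for miRNA. Normality, NRS SD 2, the correlations, the classes and d = 0.39 are all assumptions of this check and not figures from the protocol.

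**What to change.** Replace the chi-square sentence in section 2.12.2 with three rules:

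1. Baseline miRNA, cases against controls: a t-test or linear regression on normalised expression, or a Mann-Whitney test if the data are not normal.
2. NRS and the secondary scales over visits: a linear mixed model for repeated measures, or Friedman and paired rank tests if the data are not normal, reporting the estimated change from baseline.
3. Chi-square: categorical baseline variables only.

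Amend the preceding sentence so that it no longer calls the case-control miRNA comparison a repeated measure. The covariance structure and the primary time point are for the sponsor to choose and to state before analysis.

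The cost is a rewritten paragraph and slightly more analysis work in the same software (SPSS fits mixed models). No further patients, visits or samples are needed.

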### 2.3. Study purpose

To evaluate the differential expression of miRNAs in patients with CAPS and healthy controls, to provide new biomarkers for diagnosis of CAPS.To explore the association between the changes of miRNAs and the efficacy of duloxetine treatment at week 4, 12, 24 and 36 in patients with CAPS.

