### 2.10. Outcomes measures

#### 2.10.1. Primary outcome.

The differential expression of miRNAs between CAPS groups and healthy control groups at baseline.The changes in abdominal pain scores before and after duloxetine treatment in patients with CAPS and their relationship with changes in miRNA.

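### The only test named for the repeated miRNA–pain association is plain Spearman at unadjusted P < 0.05, which has no patient or visit term, and the article does not say how the visits enter

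*Protocol article*

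**What the plan says.** The second primary outcome in section 2.10.1 is "The changes in abdominal pain scores before and after duloxetine treatment in patients with CAPS and their relationship with changes in miRNA". Section 2.3 fixes the time points: the "association between the changes of miRNAs and the efficacy of duloxetine treatment at week 4, 12, 24 and 36 in patients with CAPS". Table 1 marks the pain rating scale and miRNA at all five visits, so each patient contributes up to four changes from baseline, three of them up to the end of treatment.

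Section 2.12.2 recognises this structure: "Whole data of primary and secondary outcomes are repeated measure and continuous data". A few sentences later it names the method for the association: "The association of blood biomarkers, plasma concentration, genotype and clinical efficacy, medication adherence will be assessed by Spearman correlation analysis". Significance is P < 0.05, with no adjustment mentioned. No mixed model, GEE or repeated-measures correlation is named, and nothing says whether visits are pooled, tested one by one, or reduced to one value per patient.

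**The concern.** Spearman's test assumes independent pairs. Changes at several visits of one patient are not independent, because all are measured from the same baseline. A test without a patient or visit term can be applied here by pooling visits, by testing each visit separately, or by reducing each patient to one value. These choices have different error rates and power, and the article picks none of them.

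This is the only named analysis that links miRNA to duloxetine response, so the article's claim to find a predictor of efficacy rests on it. The error rates below are per miRNA, before any multiplicity across miRNAs.

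**Working it through.** **Inputs from the article.** Two-sided alpha 0.05, power 0.95 and 172 patients (section 2.12.1); 20% loss, giving 215 (section 2.12.1); m = 3 or 4 post-baseline visits (section 2.3, Table 1). The article gives no correlation between miRNA change and pain change and no within-patient correlation, so both are assumed below.

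**The plan's own figure.** 172 / (1 − 0.20) = 215, as stated. The 172 cannot be reproduced because no effect size or test is given. If it was meant for a correlation, r of about 0.27 fits: ((1.960 + 1.645) / atanh 0.27)² + 3 gives 173 after rounding up.

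**Correlation between two changes of one patient.** With equally correlated visits (correlation ρ, common variance), the covariance of Y_t − Y_0 and Y_s − Y_0 is σ²(1 − ρ) and each variance is 2σ²(1 − ρ). The correlation is 0.5 whatever ρ is.

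**Reading 1: visits pooled.** The design effect is 1 + (m − 1) × ICC_x × ICC_y.
- m = 3: 1 + 2 × 0.5 × 0.5 = 1.50. The true error is 2 × (1 − Φ(1.96 / √1.50)) = 11.0%.
- m = 4: 1 + 3 × 0.5 × 0.5 = 1.75. The 688 pairs are worth 688 / 1.75 = 393, and the true error is 13.8%.
- Simulation with 172 patients gave 10.0–11.1% (m = 3) and 12.6–13.6% (m = 4). Varying both ICCs from 0.3 to 0.7 gave 6.7–15.9% and 8.0–20.8%.
- Genotype, named in the same sentence, is constant within a patient (ICC_x = 1). If it were pooled, the design effects would be 2.0 and 2.5 and the error 16.6% and 21.5%.

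**Reading 2: each visit tested, any P < 0.05 counted.** Each test alone is valid (about 5%). The simulated chance of at least one false positive is 14% for three visits and 18% for four.

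**Reading 3: one visit only.** The error is about 5%. The table compares its power with that of a repeated-measures analysis of all visits, assuming the same slope within and between patients:

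| True r | One visit, Spearman | All visits (3 / 4) |
|---|---|---|
| 0.10 | 24% | 61% / 75% |
| 0.15 | 45–47% | 92% / 97% |
| 0.20 | 72% | over 99% |
| 0.27 | 93% | about 100% |

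**Does a better method exist whatever the form of the link?** At r = 0.15:
- If the link is purely between patients, an exchangeable model with one miRNA coefficient has only 34–42% power, below the 46–48% of one-visit Spearman.
- Spearman on each patient's mean change reaches 82–86% in that case, but only about 45% when the slopes are equal, because the shared baseline noise remains.
- A patient-clustered model with working independence and robust standard errors has 81–86% power in both cases, against 45–48% for one-visit Spearman, with error near 5.5%.

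**The case against.** The strongest reply is that the article never says visits will be pooled. Listing four weeks reads naturally as four separate analyses, and a before-and-after change reads naturally as one value per patient. Either way, each Spearman test uses independent patients and is valid. That stands: the 10–14% figure depends on pooling, and a reader who infers that the plan will pool goes beyond the text. The same holds for the genotype figures.

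A reader might also infer that Spearman wastes about half the power. The documents do not support that as a general statement. It is roughly right only for r of about 0.10–0.15 with equal slopes within and between patients; the loss is about 28 points at 0.20 and about 7 at 0.27. If the link is between patients, which is what a predictor of response concerns, an exchangeable model can do worse than one-visit Spearman, and Spearman on a per-patient mean does well.

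Finally, this is a condensed article, and its analysis plan may settle how the visits enter. That would excuse silence about a method. Here the method is stated, in the same paragraph that calls the data repeated measures, and it does not fit that structure without a further rule. Separate tests at the four weeks, the most natural reading, still meet an unadjusted threshold.

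**Conclusion.** The point holds in limited form. The stated test does not account for the repeated structure that the plan itself describes. Its false-positive rate per unrelated miRNA is about 10–14% if visits are pooled and about 14–18% if any of three or four unadjusted visit tests counts. One prespecified visit or per-patient summary would be valid, but none is named, a single visit would not cover the four weeks in section 2.3, and the power lost depends on a correlation that the article does not give.

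These figures assume 172 evaluable patients, equally correlated visits and a shared baseline; the modelled comparisons did not include a baseline-score term. The change is worth making because a better-suited analysis is cheap, not because the planned one is certain to mislead.

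**What to change.** In section 2.12.2, make the test of each miRNA one patient-clustered model. The outcome is change in the score at each visit; the terms are change in miRNA at that visit, visit as a factor, and the baseline score. Fit it by GEE with working independence and robust standard errors, and report the miRNA coefficient with its 95% confidence interval. Alternatively, split the miRNA change into each patient's mean and the deviation from it, so that between- and within-patient associations are estimated separately. Use ranks or logs if the data are skewed. Apply the same model to the secondary scales.

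Keep Spearman as a per-visit description and state that it never pools visits. Analyse genotype with one record per patient or in the same clustered model.

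The cost is a wording change and slightly more analysis work, with no new data, visits or patients; the named package can fit these models. Working independence gives up some power against an exchangeable model when the within- and between-patient slopes are equal (81–86% against 92–97% at r = 0.15).

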### 2.6. Intervention

#### 2.6.1. Drugs.

The property of duloxetine (produced by LILLY DEL CARIBE, Inc) is white or off-white enteric-coated granules. 30 mg capsule: white opaque capsule body and blue capsule cap, 30 mg printed on the capsule; 60 mg capsule: white opaque capsule body and blue capsule cap, 60 mg printed on the capsule. Package: aluminum blister pack, 7 capsules per box, 14 capsules per box, 28 capsules per box.

Withdrawal of medications must be taper to complete withdrawal, and monitor the withdrawal response. If intolerance, return to the previously dose, and then reduction with lesser dose. Duloxetine should be swallowed, not chewed or crushed.

All drugs use was recorded by Hospital information system. All scales and scores were recorded and saved by computer, which were used to evaluate intervention.

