**Figure 2. F2:**
[figure not shown]
Study procedure. ADR = adverse drug reaction, BP = blood pressure, Cmax = maximum serum concentration, GAD7 = Generalized Anxiety Disorder7, HAMA = Hamilton anxiety scale, HAMD = Hamilton depression scale, HR = heart rate, NRS = numerical rating scale, PHQ9 = patient health questionaires 9, PRS = pain relief scale, PSQI = Pittsburgh sleep quality index, QoL = quality of life, SF36 = short form 36.

After the initial visit, every patient starts to take duloxetine under the instruction of gastroenterologist. The initial dose is 30 mg qd. After 1 week, if tolerated, increase dose to 60 mg qd, or 30 mg qd continued. In the duration of therapy, altering dose of duloxetine based on pain relief scale (PRS) score. We suggest adding 30 mg every 2 weeks, however, the total dose should not exceed 120 mg qd.

During the treatment period, patients need to have 3 outpatient visits as follow-up including 1 month (visit 2), 3 month (visit 3) and 6 months (visit 4) after the treatmet, respectively. Patients will be required to complete the same questionnaires as at the initial visit and 2 additional questionnaires, including PRS and Morisky questionnaire. Biochemical indicators, Maximum serum concentration of duloxetine, blood miRNA will be tested in the laboratory of Ruijin Hospital. Adverse drug reaction will also be recorded.

After 24-week treatment period, there is a further 12-week outpatient post-treatment follow-up period. At the terminal visit (visit 5), patients will be required to complete all the rating scales except Morisky questionnaire. Adverse drug reaction will also be recorded. Micro RNA, genotype and blood routine will be tested again.

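### Raw duloxetine concentration is rank-correlated with efficacy although the dose is altered by pain relief, so the coefficient can be shrunk or reversed

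*Protocol article*

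**What the plan says.** All from the protocol article.

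- **Analysis (section 2.12.2).** One method is named for all these associations: "The association of blood biomarkers, plasma concentration, genotype and clinical efficacy, medication adherence will be assessed by Spearman correlation analysis". The section mentions no dose, dose history or earlier relief in this analysis.
- **Dosing (section 2.7).** After the first week: "After 1 week, if tolerated, increase dose to 60 mg qd, or 30 mg qd continued". Then: "In the duration of therapy, altering dose of duloxetine based on pain relief scale (PRS) score". The direction and limit follow: "We suggest adding 30 mg every 2 weeks, however, the total dose should not exceed 120 mg qd".
- **Role of the PRS (section 2.11.1).** "PRS: To evaluate whether duloxetine dose adjustment was required".
- **Timing (section 2.7 and Table 1).** At the visits in months 1, 3 and 6, "Maximum serum concentration of duloxetine, blood miRNA will be tested in the laboratory of Ruijin Hospital". Relief-guided dosing can have begun by then.
- **Outcomes (sections 2.10.1 and 2.10.2).** The relation of pain change to miRNA change is a primary outcome. Concentration against efficacy is not a listed outcome.
- **Dose records (section 2.6.1).** "All drugs use was recorded by Hospital information system".

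**The concern.** Dose is not fixed by design. It follows the patient's earlier relief, and the only adjustments described after week 1 are upward. A patient with little relief is therefore likely to be on a higher dose, and to have a higher concentration, when blood is drawn. Patients who respond poorly early also tend to respond poorly later. Together these give a negative association between concentration and relief that has nothing to do with what the drug does.

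A rank correlation has no term to separate this feedback from a true exposure-response relation. The study could report that higher exposure goes with less benefit when exposure has no effect, or when it helps. A miRNA that reacts to drug exposure would carry part of the same artefact and could be taken for a marker of non-response.

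**Working it through.** **Sample size used.** The article's own figure reproduces: 172 / (1 - 0.20) = 215 patients. The checks use the 172 evaluable patients. At that size, a Spearman coefficient reaches two-sided P < 0.05 at about 1.96 / sqrt(171) = 0.15 in absolute value.

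**From the documents.** Steps of 30 mg, ceiling 120 mg, dose decided by PRS.

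**Assumed (not in the documents).** All patients start at 60 mg. There are up to two 30 mg steps, each taken when relief is below a target. The spread of response, the spread of clearance and the size of the exposure effect are varied. Patients who stay on 30 mg are not modelled.

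**Model A (effect per doubling of exposure).** Concentration = dose × k, where log k has SD 0.35 or 0.5 between patients. Relief = patient's own response (SD 1 or 2 points) + b × log2(concentration / 60) + noise.

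- *No exposure effect (b = 0).* The truth is 0. Over these settings the mean raw Spearman was about -0.24 to -0.50, with P < 0.05 in 91% to 100% of simulated trials. Dose-normalised concentration gave about 0.
- *Real effect.* Mean Spearman of relief with:

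| b (points per doubling) | Response SD | Log-SD of k | Concentration, everyone on one dose | Raw concentration, titrated | Concentration / dose, titrated |
|---|---|---|---|---|---|
| 0 | 2 | 0.5 | 0.00 | -0.38 | 0.00 |
| 1 | 2 | 0.5 | +0.29 | -0.10 | +0.28 |
| 2 | 1 | 0.5 | +0.69 | sign stays positive | about +0.54 |

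At 1 point per doubling and response SD 1, the raw coefficient also kept the right sign (+0.19 to +0.23).

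**Why normalising works, and where it falls short.** Concentration / dose = k, which titration does not alter, so the feedback drops out. It understates a strong effect because patients with low k respond less, are moved up, and so catch up in exposure.

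**Model B (linear effect, separate check).** Relief = patient's own response + b × concentration / 30 + noise (SD 0.5), log-SD of k 0.3, 400 trials per setting. Mean Spearman of concentration with relief, fixed dose → titrated:

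| b (points per 30 mg-equivalent) | Response SD 0.5 | Response SD 1 | Response SD 2 |
|---|---|---|---|
| 0.25 | +0.21 → +0.01 | +0.13 → -0.34 | +0.07 → -0.55 |
| 0.5 | +0.38 → +0.27 | +0.26 → -0.12 | +0.14 → -0.44 |
| 1.0 | +0.63 → +0.53 | +0.46 → +0.22 | +0.28 → -0.21 |

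The coefficient is shrunk in all nine cells, reversed in five, about zero in one, and still clearly positive in three.

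**miRNA change against pain relief.** Two kinds of miRNA behave differently.

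- *Tracks exposure (assumed r = 0.5), no link to relief, no exposure effect.* Mean Spearman was -0.10 to -0.24, falsely significant in 29% to 89% of trials. Conditioning on current dose returned it to about 0.
- *Truly marks response, independent of exposure (log-SD of k 0.5).* The unadjusted coefficient is nearly right, and conditioning on dose damages it:

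| b (points per doubling) | Response SD | Fixed dose | Unadjusted, titrated | Conditioned on current dose |
|---|---|---|---|---|
| 0 | 2 | 0.43 | 0.43 | 0.22 |
| 1 | 2 | 0.41 | 0.38 | 0.20 |
| 1 | 1 | 0.30 | 0.26 | 0.17 |

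Relative to the unadjusted value, the loss is 1 - 0.22/0.43 = 49%, 1 - 0.20/0.38 = 47% and 1 - 0.17/0.26 = 35%.

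A *baseline* miRNA linked to response was attenuated in Model B (for example +0.31 to +0.18) but did not change sign.

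**The case against.** **Not an endpoint.** Concentration against efficacy appears in no hypothesis, purpose or outcome. It stands only in the schedule, the list of tests and one analysis sentence. This is correct and limits the weight of the point.

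**The primary miRNA result.** A reader might infer that the primary miRNA-pain association is equally compromised. The documents do not support that. The artefact needs a miRNA that responds to exposure. The Discussion (section 3) cites miRNAs that changed after duloxetine treatment in depression, so this is possible, but it is not shown for the miRNAs studied here. Nor is adding dose as a covariate a plain correction: dose is itself a consequence of response, and the covariate can remove about half of a true signal.

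**Reversal is not certain.** A strong exposure effect with little spread in response keeps the sign. What stands is that the coefficient *can* reverse.

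**The direction of titration is inferred.** The article says that PRS alters the dose and that the suggested steps are upward. It does not say in words that poor relief triggers a step. The rule is probably in Figure 1.

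**Adjustment may be in an analysis plan not shown.** It may be, but this article names a method, and that method does not fit its own dosing scheme.

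**Two further readings do not hold.** A reader might conclude that the Cmax is not a true maximum because no sampling time is given. A condensed article commonly leaves draw times to the full protocol, so this is not shown. A reader might also say that ranking genotype has no meaning. An ordered allele count can be ranked; only an unordered genotype cannot.

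**Conclusion.** The point holds for plasma concentration against efficacy. The stated method treats concentration as if it were independent of earlier relief, while the dosing scheme makes it depend on it. With no exposure effect, the expected coefficient is about -0.24 to -0.50 rather than 0, and nearly always significant. A real positive effect is shrunk, and reversed when patients differ widely in response.

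These sizes rest on assumed response spread, clearance spread and step rule, and on poor relief raising the dose. The direction of the bias follows from that last inference. Its size does not follow from the documents.

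For the primary miRNA association the consequence is conditional, and the unadjusted Spearman is the better main analysis. The correction is worthwhile because it is cheap, but it does not invalidate a listed outcome.

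**What to change.** In section 2.12.2:

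1. **Concentration and efficacy.** Correlate or regress efficacy on dose-normalised concentration (concentration divided by the dose at that visit), one visit at a time. Use the Numerical Rating Scale (NRS) score at the visit as the outcome, adjusted for baseline NRS. A lower score means less pain, so a beneficial effect has a negative slope.
2. **Raw concentration.** Label any raw concentration-efficacy correlation as descriptive, and state that dose follows PRS.
3. **miRNA change and pain change.** Keep the unadjusted Spearman as the main analysis. Add a version conditioned on current dose as a sensitivity analysis only, stating that it can weaken a true response marker.
4. **Genotype.** If it is an unordered category, compare efficacy across its levels as a factor.

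**Cost.** Analysis wording only, since drug use is already recorded (section 2.6.1). Dose-normalising assumes concentration roughly proportional to dose, and it understates a strong exposure effect (for example 0.54 against 0.69). No change to the dosing rule is implied.
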